#### Secondary outcomes

1. Placental abruption (clinically or on placental examination), which is determined at the time of delivery.

2. SGA (
<
 5
${\;}^{\text{th}}$
 centile) requiring delivery at 
<
 34 wk and 
<
 37 wk, which is measured by ultrasound.

3. Stillbirth or IUFD at 
≥
 20 wk, which is determined by ultrasound.

4. Spontaneous preterm delivery at 
<
 34 wk and 
<
 37 wk, which is determined by clinical examination and ultrasound.

5. Respiratory distress syndrome, described as the requirement for surfactant and ventilation due to prematurity, which is diagnosed by examination at the time of birth.

6. Ventilation requirement is defined as the need for positive pressure.

7. Neonatal intensive care unit admission, which is diagnosed by examination at the time of birth.

8. Neonatal anomaly, especially gastroschisis.

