During the trial, some participants may be excluded from the study due to reasons such as abortion or IUFD below 20 wk of gestation or major fetal abnormalities or side effects of aspirin or discontinue the intervention. We will use the CONSORT checklist when writing our report.

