#### Gathering of side effects and adverse incidents

Side effects are defined as any unwanted drug complications including hypersensitivity reactions, bleeding complications, headache, dizziness, nausea, vomiting, etc. Adverse events are defined as hospitalization for maternal and fetal observation, including bleeding course, spontaneous PTL, premature rupture of membranes, abortion, stillbirth, and the termination of pregnancy for fetal or maternal indications. Thirty days after the start of aspirin administration, a follow-up telephone interview was conducted with the participants to assess side effects and adverse events. If these events are considered a part of the normal development of the corresponding pregnancy, they will not be included in the category of drug-related complications but will be recorded in the clinical electronic records of the participants. If it is necessary to stop the drug permanently, the data will be placed in the data proportion of the discontinuation and will be removed from the final analysis.

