### Monitoring

During the trial, some participants may be excluded from the study due to reasons such as abortion or IUFD below 20 wk of gestation or major fetal abnormalities or side effects of aspirin. In case of severe side effects and the need to discontinue the drug, the data will be placed in the data proportion of the discontinuation and will be removed from the final analysis. Since the trial is not blind for the researchers, they can access the results at any stage, due to the nature of the intervention.

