### Safety considerations

A physician assesses the possible role of the LDA if there are any significant adverse effects within therapy. If it is approved, the patient will be omitted from the study. Despite recording all the lost data about outcomes and follow-ups, it will not be included in the analysis. The discontinuation of treatment for pregnancies will be expressed by reason and study group.

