#### Secondary analysis

By using appropriate tests, the secondary outcomes will be compared between study groups. The p-value and 99% CI will be generated for the treatment results.

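### Neonatal anomaly is secondary outcome 8, yet major fetal abnormality is a discretionary reason for exclusion after randomisation, so cases that define the outcome can leave its comparison

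*Protocol article*

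**What the plan says.** All references are to the protocol article.

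- **Secondary outcomes, item 8:** "Neonatal anomaly, especially gastroschisis".
- **Secondary analysis:** "the secondary outcomes will be compared between study groups", with a p-value and a 99% confidence interval.
- **Intervention, closing paragraph:** reasons for exclusion during the trial include "abortion or IUFD below 20 wk of gestation or major fetal abnormalities or side effects of aspirin or discontinue the intervention".
- **Monitoring:** repeats that participants may be excluded "due to reasons such as abortion or IUFD below 20 wk of gestation or major fetal abnormalities or side effects of aspirin".
- **Exclusion criteria:** six entry criteria; fetal abnormality is not one of them.
- **Intervention:** aspirin starts before 11 wk in one arm, and after 11 wk with a cut-off of 16 wk in the other. The anomaly scan is at 18–22 wk.
- **Blinding and Monitoring:** participants and researchers know the allocation, and researchers can see results at any stage. A blinded analyser does the assessments.
- **Safety considerations:** when a physician confirms a role of aspirin in a significant adverse effect, "If it is approved, the patient will be omitted from the study"; then "Despite recording all the lost data about outcomes and follow-ups, it will not be included in the analysis". The section also promises that "The discontinuation of treatment for pregnancies will be expressed by reason and study group".
- **Gathering of side effects and adverse incidents:** adverse events include "the termination of pregnancy for fetal or maternal indications".

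**The concern.** A major fetal abnormality is both a case for outcome 8 and a permitted reason to take the woman out of the study. The exclusion comes after allocation, depends on the outcome, is discretionary, and is open to people who know the arm.

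This matters for this trial because aspirin before 11 wk is what separates the arms. The Introduction reports that earlier observational studies suggested certain birth defects, gastroschisis among them, with first-trimester aspirin. It adds that a randomised trial and other large studies found no association overall. Outcome 8 is where this trial could add randomised evidence of its own. If the more severe cases can be set aside, few or no events on both sides would say little about whether early aspirin is safe in this respect.

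**Working it through.** **1. Is the exclusion after randomisation?** Yes. It is described as happening during the trial and is not an entry criterion. The scan at 18–22 wk falls after aspirin has started in both arms (latest start 16 wk).

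**2. Does the text remove these cases from the analysis?** Not in so many words.
- Intervention and Monitoring say that such participants may be excluded from the study. Removal from the analysis is the natural reading, but it is an inference.
- The explicit sentence in Safety considerations that recorded data are left out of the analysis follows adverse effects that a physician attributes to aspirin. It would reach an anomaly only if the anomaly were so attributed.
- The removal sentences in Monitoring and in Gathering of side effects concern stopping the drug.
- No sentence keeps outcome 8 outside the exclusion rule.

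**3. Can another provision restore the case?** The blinded analyser cannot assess a participant who has already been removed. Adverse-event records and the table of discontinuations by reason may show some cases, but not within the outcome 8 comparison.

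**4. What could it do to the result?** The plan has no figure on this point to reproduce. The only input from the documents is 986 per arm (Sample size). Everything else is assumed: an anomaly rate of 1% to 4%, and a share *r* of cases excluded of 25% to 75%.

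Cases per arm = 986 × p, and cases left = 986 × p × (1 − r). The 99% limits of the risk ratio at equal rates are the ratio multiplied and divided by exp(2.576 × √(2(1/x − 1/N))), where x = cases left and N = 986 minus cases removed.

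| p | r | cases left per arm | 99% factor |
|---|---|---|---|
| 1% | 0 | 9.86 | 3.17 |
| 1% | 25% | 7.39 | 3.80 |
| 1% | 50% | 4.93 | 5.14 |
| 1% | 75% | 2.46 | 10.15 |
| 4% | 0 | 39.44 | 1.77 |
| 4% | 25% | 29.58 | 1.93 |
| 4% | 50% | 19.72 | 2.25 |
| 4% | 75% | 9.86 | 3.17 |

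If every case is excluded, the comparison is 0 against 0.

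*Equal exclusion, true excess.* Observed rate = a(1 − r)/(1 − a·r). With true rates of 2% and 1%, the difference is 1.00 point at r = 0, 0.756 at 25%, 0.508 at 50% and 0.256 at 75%. The ratio stays at 2.00–2.02.

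*Unequal exclusion, no true effect.* Take 75% excluded in one arm and 25% in the other.
- At 1% in both arms: 0.0025/0.9925 = 0.00252 against 0.0075/0.9975 = 0.00752, a ratio of 0.34.
- At 4% in both arms: 0.01/0.97 = 0.01031 against 0.03/0.99 = 0.03030, again 0.34.

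With the arms swapped, the ratio is about 3. The documents do not say whether exclusion would differ by arm, or in which direction.

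*Complete capture.* The 99% half-width of the difference is 2.576 × √(2p(1 − p)/986): 1.15 points at 1% and 2.27 points at 4%.

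**The case against.** The strongest reply has four parts.

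- **The rule is permissive.** Some women with a scan-detected abnormality may stay in, and anomalies first found at birth are not touched by the scan. This stands, and it limits the claim to what can happen. Discretion under open allocation is still no safeguard.
- **Terminations have no neonate whatever the exclusion rule says, and they are not lost.** They are defined as adverse events, and Table II has an adverse-event item. This also stands. Widening item 8 to fetal anomalies is an improvement to the definition, separate from repairing the contradiction.
- **The harm is mainly lost precision.** Equal exclusion leaves the ratio near 2.0, and the illustrated 1-point excess is below the 99% half-width even with complete capture (1.15 points at 1%). This stands for equal exclusion. It does not answer unequal exclusion, which a confidence interval would not reveal.
- **The outcome is minor.** It is absent from the secondary objectives and listed last, and the Introduction ends on reassuring evidence. That lowers the priority but does not resolve the conflict.

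Two stronger readings are tempting and not supported. A reader might take the non-analysis sentence in Safety considerations as an order to discard every fetal-abnormality case; its subject is adverse effects attributed to aspirin. A reader might also conclude from Table II and the outcome-gathering list, neither of which names anomaly, that it will not be collected. The article is condensed, the electronic case report form is not shown, and examinations, imaging and delivery data are said to be recorded.

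**Conclusion.** The conflict is in the current text: outcome 8 is to be compared between arms, and the event it counts may remove a participant after randomisation. Its effect on the analysis rests on reading exclusion from the study as exclusion from the analysis, with no exemption stated for outcome 8.

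The size of the effect cannot be derived from the documents. Under the assumed rates, equal exclusion costs events and absolute difference but not the ratio, while unequal exclusion could move the ratio a long way in either direction. Neither an arm imbalance nor an actual loss of cases has been shown. The point should be corrected: it concerns a secondary safety outcome, and the repair is cheap.

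**What to change.** 1. In Intervention and Monitoring, state that major fetal abnormality is not a reason for exclusion from the outcome 8 analysis. In Safety considerations, state that the omission rule does not apply to this outcome.
2. Word item 8 as fetal or neonatal major structural anomaly, so that terminated pregnancies can count.
3. Count by allocated arm every such anomaly identified at the 18–22 wk scan, at termination for fetal indication where documented, or in the delivery or newborn record. Show gastroschisis separately.
4. Report pregnancies lost before the scan by arm as not assessable. They have neither scan nor newborn record, so full capture cannot be promised.

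The cost is minor record tracing for terminated or excluded pregnancies, plus a statement that outcome 8 uses a wider analysis set than outcomes still subject to the exclusion rules. No new procedure or additional participants are needed. The change removes outcome-dependent exclusion; it does not make the comparison precise for rare defects.

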### Gathering of outcomes

#### Gathering of pregnancy and neonatal outcomes

Data related to delivery and newborns will be collected through the patients and the hospital maternity records. The outcome of the participants will be assessed in terms of the incidence of early and late-onset PE, placental abruption, stillbirth, spontaneous premature delivery, postpartum hemorrhage, birth weight, infant respiratory distress at birth, need for mechanical ventilation, and admission to the NICU. If neonates are admitted to the NICU, neonatal outcomes will be collected from the discharge summary of the NICU.

#### Gathering of side effects and adverse incidents

Side effects are defined as any unwanted drug complications including hypersensitivity reactions, bleeding complications, headache, dizziness, nausea, vomiting, etc. Adverse events are defined as hospitalization for maternal and fetal observation, including bleeding course, spontaneous PTL, premature rupture of membranes, abortion, stillbirth, and the termination of pregnancy for fetal or maternal indications. Thirty days after the start of aspirin administration, a follow-up telephone interview was conducted with the participants to assess side effects and adverse events. If these events are considered a part of the normal development of the corresponding pregnancy, they will not be included in the category of drug-related complications but will be recorded in the clinical electronic records of the participants. If it is necessary to stop the drug permanently, the data will be placed in the data proportion of the discontinuation and will be removed from the final analysis.

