### Blinding

Due to the nature of the intervention, neither participants nor researchers could be blinded to allocation. However, assessments will be conducted by a blind analyzer for trial allocation.

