**Delivery, neonate data, and outcomes**	
**18**	Gestational diabetes under insulin
**19**	Gestational diabetes without insulin
**20**	Weight gain during the 1 ${\;}^{\text{st}}$ trimester
**21**	Weight gain during the 2 ${\;}^{\text{nd}}$ trimester
**22**	Weight gain during the 3 ${\;}^{\text{rd}}$ trimester
**23**	Total weight gain
**24**	Gestational age at delivery
**25**	Birth weight
**26**	Postpartum hemorrhage
**27**	Drug-related side effects and adverse events
**28**	Placenta abruption
**29**	Early-onset PE
**30**	Late-onset PE
**31**	The requirement for NICU admission or mechanical ventilation
**32**	Neonatal respiratory distress syndrome
**33**	Hospitalization for maternal and fetal observation
**34**	Spontaneous PTL < 34 wk
**35**	Spontaneous PTL < 37 wk
**36**	IUFD or stillbirth > 20 wk
APs: Anti-phospholipid syndrome, SLE: Systemic lupus erythematosus, PE: Pre-eclampsia, BMI: Body mass index, IVF: In vitro fertilization, SGA: Small for gestational age, PTL: Preterm labor, PAPP-A: Pregnancy-associated plasma-A, UtA-PI: Uterine artery pulsetillity index, NICU: Neonatal intensive care unit, IUFD: Intrauterine fetal demise	

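### As defined, early bleeding and early pregnancy loss managed without admission are not captured alike in the two arms

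*Protocol article*

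**What the plan says.** The section Gathering of side effects and adverse incidents sets up two safety categories. The first is tied to admission: "Adverse events are defined as hospitalization for maternal and fetal observation, including bleeding course, spontaneous PTL, premature rupture of membranes, abortion, stillbirth". Pregnancy termination is listed too. The second is tied to the drug and has no admission condition: "Side effects are defined as any unwanted drug complications including hypersensitivity reactions, bleeding complications, headache, dizziness, nausea, vomiting, etc".

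A judgement is then applied: "If these events are considered a part of the normal development of the corresponding pregnancy, they will not be included". The rest of that sentence confines the rule to the drug-related label and keeps such events in each woman's electronic file. The same section places a telephone interview for side effects and adverse events 30 days after aspirin is started. The Intervention section adds that participants are asked about possible side effects of aspirin. It also sets the exposure: before 11 wk in the intervention arm, after 11 wk and no later than 16 wk in the control arm.

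On attribution, Safety considerations says: "A physician assesses the possible role of the LDA if there are any significant adverse effects within therapy". If aspirin's role is confirmed, the woman is dropped, and her data are recorded but not analysed. Under Blinding, "neither participants nor researchers could be blinded to allocation"; a blinded analyser carries out assessments, but nothing assigns safety attribution to that person.

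In Table 2, item 27 reads "Drug-related side effects and adverse events". Item 33 is hospitalization for observation, item 26 postpartum hemorrhage, item 28 abruption, items 34 and 35 spontaneous preterm labour, and item 36 fetal death or stillbirth after 20 wk.

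**The concern.** The trial's arms differ in exposure mainly in the weeks before controls start aspirin. Those are also weeks in which bleeding and miscarriage matter for safety. The Exclusion criteria bar entry to women with vaginal bleeding or a significant hematoma, and the adverse-event definition lists bleeding and abortion.

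A safety comparison needs a definition that can be met equally in both arms. Here one category requires admission and the other requires a link to a drug that one arm is not yet taking. If early bleeding and loss are counted under these definitions, the arms can differ when aspirin has no effect. A real excess in the early arm can also be hidden if the events are put down to normal pregnancy.

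**Working it through.** No figure in the article bears on this point, so the check sets the rules side by side.

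**1. Where an early bleed or loss falls, before the control woman starts aspirin**

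| Bleed or loss before 20 wk | Intervention arm, on aspirin | Control arm, not yet on aspirin |
|---|---|---|
| Admitted | Adverse event; item 33 | Adverse event; item 33 |
| Not admitted, attributed to aspirin | Side effect; item 27 | Cannot arise |
| Not admitted, not attributed | Neither category; clinical record only | Neither category; clinical record only |

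The first row is symmetric. The asymmetry lies in the second row and ends once the control woman starts aspirin.

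**2. Length of that window.** It is s − e, where s is the control start (11 to 16 wk, Intervention section) and e is the gestational age at randomisation. The article does not fix e beyond requiring that the intervention arm start before 11 wk. Assuming e of 6 to 7 wk gives 11 − 7 = 4 to 16 − 6 = 10 weeks. Assuming e = 10 wk and s = 11 wk gives 1 week.

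**3. Timing of the call.** Thirty days is 4 wk 2 d.
- Intervention: start before 11 wk, so the call falls before 15 wk 2 d.
- Control: start after 11 and up to 16 wk, so the call falls after 15 wk 2 d and up to 20 wk 2 d.

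The two calls do not overlap in gestational age. A control woman who miscarries before starting aspirin never starts the 30-day clock.

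**4. The form.** Table 2 has no item for antenatal bleeding (item 26 is postpartum) and none for loss below 20 wk (item 36 begins after 20 wk). The secondary outcome on stillbirth or fetal death also begins at 20 wk. Events outside hospital are therefore left to item 27, whose wording begins with drug-related.

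**5. The judgement.** No criteria are given for what is normal for a pregnancy. Researchers and participants know the arm. The causality review covers effects during therapy, so it has nothing to review in a control woman before aspirin.

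**6. Direction of the error, if early unadmitted events were counted only through these categories.** Let p be the risk of such an event in the window in controls, d the true excess in the intervention arm, and a the share attributed to aspirin.
- Counted in the intervention arm: a(p + d). Counted in controls: 0.
- Counted difference: a(p + d). True difference: d.

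With d = 0 the counted difference is a·p, a spurious excess whenever a is above zero. With d above zero and a small, a(p + d) can fall below d. The article gives none of p, d or a, so neither size nor sign can be derived.

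**7. Removal.** The Intervention and Monitoring sections allow exclusion for abortion or fetal death below 20 wk, major fetal abnormality and aspirin side effects. Permanent discontinuations, and women whose adverse effect is attributed to aspirin, are taken out of the analysis. Even a correctly recorded early loss or attributed bleed may therefore not reach a comparison.

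**The case against.** A good deal can be said for the plan.

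- **Events are not discarded.** A reader who stops at the first half of the normal-pregnancy rule might infer that they are. The sentence withholds only the drug-related label and keeps the event in the electronic record; the Data collection section also says unusual events are recorded. An all-cause comparison could be rebuilt from those records where the event was noticed. This stands. It does not help an unadmitted bleed or loss that no visit or call brought to light.
- **Capture is not limited to admissions.** Bleeding side effects need no admission. This stands, but only for women whose bleed can be called a drug complication.
- **Much of the form is free of attribution.** Items 28 and 33 to 36 carry none, and neonatal anomaly, the harm discussed in the Introduction, is a secondary outcome to be compared by arm. So the inference that the arms cannot be compared on any early harm is not supported. What remains is bleeding and loss before 20 wk without admission.
- **No stated analysis compares drug-related rates.** The only by-arm safety statement is that discontinuations are reported by reason and group. A reader might infer that the plan will set the early arm's drug-related rate against a control rate that is zero by construction; the article does not say so. Full safety tables may sit in documents not shown. The definitions, the call and the form items are stated here, however, and determine what those tables can contain.
- **Unblinded attribution is an inference.** It is a fair one in an open trial, but the article states only that researchers know the arm, not who judges each event.
- **A loose reading of the adverse-event list** could take abortion or bleeding as events in their own right. The sentence ties them to hospitalization, and item 33 repeats that.

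**Conclusion.** The point holds in a limited form. As defined, vaginal bleeding and pregnancy loss before 20 wk managed without admission are captured differently in the two arms during the weeks before controls start aspirin. The reasons are the two category definitions, a safety call timed from aspirin start, a judgement without criteria or stated blinding, and a form without the two relevant items.

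The size of the bias cannot be computed. A reader might apply an assumed 10–20% rate of early bleeding or loss to the planned 986 per arm, giving 986 × 0.10 = 99 to 986 × 0.20 = 197 events per arm, and treat them as miscounted. The documents do not support that step. They give no such rate, exclude women already bleeding at entry, cover admitted cases in item 33, and do not say what share would be attributed. The 4 to 10 week window likewise rests on assumed entry at 6 to 7 wk and may be shorter.

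The conclusion assumes that the definitions are applied as written. It concerns the safety comparison, not the pre-eclampsia endpoint. It should be corrected, and the correction is cheap.

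**What to change.** 1. Define these adverse events by the event itself (any vaginal bleeding or hematoma, any pregnancy loss at any gestation), whether or not the woman is admitted.
2. Record them from randomisation over the same gestational window in both arms, including the weeks before controls start aspirin, and set safety contacts by gestational age or time since randomisation, not by aspirin start alone.
3. Add two items to Table 2: antenatal bleeding or hematoma, and pregnancy loss with gestational age.
4. Compare the randomised arms on all such events regardless of attribution. Keep the drug-related judgement, with the normal-pregnancy rule confined to it, as a descriptive column only.
5. State that this comparison includes women whom the Intervention, Gathering of side effects and adverse incidents, Monitoring and Safety considerations sections would otherwise exclude or remove: loss below 20 wk, major fetal abnormality, attributed side effect, and discontinuation.

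The changes affect recording and reporting only. They need wording in those sections and two form items. The downside is longer adverse-event tables. For women already enrolled, events kept in the clinical record can be entered retrospectively, but those that went unnoticed cannot be recovered that way.

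### Women who must stop aspirin are removed from the final analysis after randomisation, so the primary comparison is not of the groups as randomised

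*Protocol article*

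**What the plan says.** The removal rule appears in three sections of Materials and Methods, and a fourth section touches on it.

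- Gathering of side effects and adverse incidents: once permanent stopping is necessary, "the data will be placed in the data proportion of the discontinuation and will be removed from the final analysis".
- Monitoring: the same consequence follows "In case of severe side effects and the need to discontinue the drug".
- Safety considerations: a physician judges whether aspirin played a role in a significant adverse effect. "If it is approved, the patient will be omitted from the study". The section continues: "Despite recording all the lost data about outcomes and follow-ups, it will not be included in the analysis".
- Intervention: the reasons for which some women may be excluded include "side effects of aspirin or discontinue the intervention".

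Statistical analysis compares intervention with control and names no analysis set that overrides this. Safety considerations does promise a breakdown of discontinuations by reason and by arm.

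Two features of the design matter. Under Intervention, the early arm starts aspirin before 11 wk, ideally once a fetal heartbeat is seen. The control arm starts after 11 wk and no later than 16 wk, and both continue to 36 wk or premature delivery. Under Blinding and Monitoring, participants and researchers know the allocation, and researchers can see results at any stage.

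**The concern.** Randomisation makes the two groups comparable as assigned. A rule that drops women because of what happens to them on treatment replaces those groups with women who tolerated their assigned schedule. That holds even when equal proportions are dropped, because tolerating aspirin from early pregnancy and tolerating it from a later start need not select the same women.

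In this trial equal proportions are also unlikely, because the arms differ in when aspirin starts. If women taken off aspirin differ from the rest in pre-eclampsia risk, unequal removal can create an apparent effect of early aspirin or hide a real one.

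**Working it through.** **1. Time at risk of removal.** From the start and end weeks under Intervention, and assuming 6 wk for a visible fetal heartbeat (the protocol gives no week):

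- Early arm: 36 − 11 = 25 to 36 − 6 = 30 weeks of planned aspirin.
- Control arm: 36 − 16 = 20 to 36 − 11 = 25 weeks.

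The early arm therefore has about 0 to 10 more weeks in which an aspirin effect can lead to removal. Until a control woman starts, that route to removal is closed to her.

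**2. The plan's own figure.** Sample size gives 4.3% vs 1.6%, 90% power, alpha 5%, 896 per arm, and 986 with a 10% allowance for loss to follow-up. The two-sided two-proportion formula gives 824 per arm without continuity correction and 896 with it, which matches. 896 × 1.10 = 985.6, rounded to 986. The point does not depend on this figure, but steps 4 and 5 use 986 and the planning rates.

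**3. Bias when the multiplier k is taken against women who would not be removed.** Assume no true effect. A fraction e is removed in the early arm and c in the control arm. The same type of woman is affected in both arms, but in controls a fraction e − c of them stays in the analysis. Then

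RR = (1 − c) / [(1 − e) + (e − c)k]

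| e vs c | k = 0.5 | k = 2 | k = 3 |
|---|---|---|---|
| 10% vs 5% | 0.95/0.925 = 1.027 | 0.95/1.00 = 0.950 | 0.95/1.05 = 0.905 |
| 15% vs 5% | 0.95/0.90 = 1.056 | 0.95/1.05 = 0.905 | 0.95/1.15 = 0.826 |

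At k = 1 the ratio is 1.

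**4. Bias when k is taken against the overall risk p.** The remaining risk in an arm with removed fraction e is p(1 − ek)/(1 − e), and likewise with c in the control arm. The type I error is for a two-sided pooled z test at 5%, with p = 4.3% in both arms and 986 randomised per arm.

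| e vs c | k | RR | Type I error |
|---|---|---|---|
| 10% vs 5% | 0.5 | 1.028 | 5.2% |
| 10% vs 5% | 2 | 0.938 | 5.9% |
| 10% vs 5% | 3 | 0.869 | 8.9% |
| 15% vs 5% | 0.5 | 1.060 | 5.8% |
| 15% vs 5% | 2 | 0.869 | 9.0% |
| 15% vs 5% | 3 | 0.723 | 23.8% |

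For the last row, (0.55/0.85)/(0.85/0.95) = 0.647/0.895 = 0.723. In this model there is no bias at k = 1, or when e = c with the same k in both arms.

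**5. Cost of analysing everyone.** Suppose a fraction d of the early arm stops and then carries the 4.3% planning rate. The early-arm rate becomes 0.016(1 − d) + 0.043d. With 986 analysed per arm and an uncorrected pooled test:

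| d | Early-arm rate | Power |
|---|---|---|
| 0 | 1.600% | 94.4% |
| 5% | 1.735% | 91.5% |
| 10% | 1.870% | 87.8% |
| 15% | 2.005% | 83.1% |

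**The case against.** The strongest reply is that the text is narrower than it may look, and that the size of the bias is assumed. Several inferences that a reader might draw do not hold.

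- *Every woman who stops is deleted.* The firm wording covers necessary stopping, severe side effects and effects attributed to aspirin. Only Intervention mentions discontinuing in general, and there women may be excluded. The fate of a woman who simply chooses to stop is unclear.
- *The early arm has more ways to be removed.* The listed reasons are the same in both arms. They include "abortion or IUFD below 20 wk of gestation or major fetal abnormalities or side effects of aspirin", and the pregnancy-related ones do not depend on aspirin having started. What differs is the time during which an aspirin effect can count.
- *The harms of early aspirin disappear.* Discontinuation is to be reported by reason and arm, and the data collection form has an item for drug-related side effects. What leaves the comparison is the removed women's recorded outcomes and follow-up.
- *The attributing physician is stated to be unblinded.* The text says only that a physician assesses. Knowledge of allocation is a fair inference from Blinding and Monitoring.
- *The bias favours early aspirin.* The protocol gives neither stopping rates nor the risk of women who stop, so the direction is unknown.

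These limits stand, but they do not answer the core. A separate analysis plan may exist, but this is a rule that the protocol states, and such a plan would have to contradict it.

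**Conclusion.** The point holds and should be fixed before analysis, because the rule governs the primary comparison. As written, women who must stop aspirin, or whose adverse effect is attributed to it, leave the final analysis after randomisation, and nothing in the protocol puts them back. This departs from comparison as randomised whatever the removal rates. The later start in the control arm makes unequal removal likely, and attribution takes place in a trial whose researchers are not blinded.

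The size can only be illustrated. Under the assumed 10–15% vs 5% removal and no true effect, the distortion runs from a risk ratio of about 0.83 (0.72 under the other definition of the multiplier) to about 1.06. It is nil if removed women have average risk.

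**What to change.** Replace the removal wording in Gathering of side effects and adverse incidents, Monitoring and Safety considerations, and align Intervention with it. Suggested text: the primary analysis includes all randomised women in the arm to which they were assigned, whether or not they stopped aspirin; outcomes are collected to delivery after stopping and are used. Keep the analysis without discontinuers as a labelled per-protocol sensitivity analysis, and report stopping by reason and arm as already planned. No clinical rule on stopping aspirin needs to change.

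The cost has three parts. The first is protocol and analysis wording. The second is confirmation that outcome collection continues to delivery: Safety considerations says that outcomes and follow-up are recorded, but in one unclear sentence that comes just after the woman is said to be omitted. The third is possible dilution, which may not be trivial: under the assumptions in step 5, power falls from 94.4% to between 91.5% and 83.1%, and at 10% stopping or more it is below the planned 90%.
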